#### Control Group – Exclusion criteria.

Antenatal (at recruitment):Maternal conditions that may affect placental blood flow, such as smoking, use of illicit stimulant substances, pregestational diabetes, or chronic hypertension.Maternal depression requiring pharmacological treatment (e.g., SSRIs).Risk factors for intrauterine HI, including abnormal fetal blood flow parameters on ultrasound, abnormal CTG recordings, or the need for intrauterine transfusion (IUT).Intrapartum:Indicators of possible intrauterine infection, such as amniotic fluid leakage for more than 15 hours, spontaneous preterm delivery, diagnosed intrauterine infection, or maternal symptoms of infection.Risk factors for perinatal HI.Prolonged labor lasting more than 15 hours (counted from the onset of regular uterine contractions).Birth weight below the 10th percentile or above the 90th percentile.Apgar score less than 8 at the 1st, 3rd, 5th, or 10th minute of life.Abnormal umbilical cord blood gas analysis results, defined as pH < 7.15 or BE < −9.3 mmol/l.Postnatal:Neonatal anemia requiring a top-up transfusion within the first 24 hours of life.

The exclusion criteria for the study and control groups differ based on the principle that the control group should consist of healthy neonates without risk factors for HI. In contrast, the study group includes infants diagnosed with FGR, who inherently have a higher risk of complications. These complications, such as a low Apgar score, abnormal umbilical cord blood gas analysis parameters, or an abnormal CTG recording, are precisely the factors that serve as exclusion criteria for the control group. This approach ensures that the control group provides a valid baseline for comparison against the at-risk study group.

In patients with a singleton, full-term pregnancy who present to the labor and delivery unit and meet the inclusion criteria, without meeting the antenatal exclusion criteria (except for those related to FGR), informed written consent for testing is obtained prior to delivery. The mother is also informed that if any exclusion criteria are identified during or after delivery, the child will be disqualified from further participation in the study.

To account for the potential influence of the mode of delivery (vaginal delivery [VD] or cesarean section [CS]) on S100B protein concentration, the study aims to balance the proportion of neonates delivered by each method between the study and control groups. As recruitment progresses, the number of pregnancies delivered by VD and CS in the study group will be monitored. Recruitment in the control group will be adjusted based on the mode of delivery to ensure that the percentage of CS is similar in both groups. This approach aims to minimize any confounding effects of the delivery method on the study outcomes.

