### Objectives

The study aims to:

Determine whether the cord blood S100B protein concentration is significantly higher in neonates with prenatally diagnosed FGR compared to controls.Evaluate the correlation between S100B protein concentration and fetal blood flow parameters in the UA, UtA, DV, and MCA, as assessed by ultrasound performed within 48 hours before delivery.Evaluate the discriminatory performance of S100B concentration in relation to perinatal markers associated with fetal hypoxia (pH, BE, and lactate levels in umbilical artery blood).

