### Criteria for discontinuing participation

If a full ultrasound flow assessment becomes unfeasible due to technical issues, advanced labor, or urgent delivery indications, it will be halted. However, any partial data collected will still be analyzed.

If an umbilical cord blood sample cannot be collected after birth, the patient will be excluded from the study. Nevertheless, data from excluded patients will be retained to support further analysis and ensure a comprehensive statistical evaluation.

In cases where consent is withdrawn, any data collected up to that point will be retained and used in the study.

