### Sample size

The estimated minimum total sample size for the study is 120 patients, with 60 participants in each group. The planned sample size was determined for a two-sided comparison between two independent groups, assuming a significance level of 0.05, statistical power of 80%, and equal group sizes. The variability of the primary biomarker (S100B) was estimated based on data from a previously published reference study [12], which reported median values together with the 10th and 90th percentiles. As standard deviations were not provided, dispersion was approximated from the reported percentiles under an approximate normality assumption, following established methods for recovering variability from limited summary statistics [26,27]. In the reference study, the observed difference between group medians was 1.15. However, since group allocation in that study was performed retrospectively on the basis of cranial imaging findings (brain injury vs. no brain injury), a conservative approach was adopted in the present sample size estimation to minimize the risk of effect size overestimation. Therefore, the target detectable difference was defined as 50% of the previously reported median difference.

Based on these assumptions, the estimated required sample size was approximately 55 participants per group. Additionally, considering that up to 10% of collected samples could be non-diagnostic or otherwise non-evaluable, the planned recruitment target was increased to 60 participants per group (120 participants in total). Sample size calculations were performed using standard power analysis procedures implemented in G*Power software (version 3.1.9.4).

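### Only controls are screened out for low pH, low BE, low Apgar and other hypoxia markers, so the primary contrast cannot separate an FGR effect from the selection of non-hypoxic controls

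*Protocol article*

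**What the plan says.** Objective 1 in the protocol article (Objectives) is: "Determine whether the cord blood S100B protein concentration is significantly higher in neonates with prenatally diagnosed FGR compared to controls". Trial design describes the comparator as a group without growth disorders.

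Control Group – Exclusion criteria removes controls for several findings related to hypoxia:
- cord pH < 7.15 or BE < −9.3 mmol/l;
- "Apgar score less than 8 at the 1st, 3rd, 5th, or 10th minute of life";
- abnormal CTG or fetal flow, and other risk factors for hypoxia-ischemia.

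Study group – Exclusion criteria contains none of these. The control section says the difference is intended, because controls should be healthy, and concludes: "This approach ensures that the control group provides a valid baseline for comparison against the at-risk study group". It adds that a child found to meet an exclusion criterion during or after delivery is disqualified.

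The Introduction states that S100B concentration correlates with the severity of hypoxia. Statistical methods compares the groups by t-test or Mann-Whitney U. Adjustment (pregnancy duration, mode of delivery) is described only for relationships between two continuous variables.

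**The concern.** The groups are defined before birth, but one of them is then filtered on results known only at or after birth: cord gases and Apgar. The protocol expects S100B to follow these same results. FGR infants with the same findings stay in. A higher mean in the FGR group can then arise in two ways: FGR raises S100B, or controls with raised S100B were taken out. The unadjusted test cannot tell them apart, and the rule favours the answer that objective 1 is looking for.

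Keeping hypoxic FGR infants is not the fault, since hypoxia may be part of how FGR acts on S100B. The fault is removing hypoxic controls and still describing the contrast as FGR against a valid baseline.

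**Working it through.** **1. The plan's own scale.** Sample size describes a "two-sided comparison between two independent groups, assuming a significance level of 0.05, statistical power of 80%, and equal group sizes". It says that "the observed difference between group medians was 1.15" and that "the target detectable difference was defined as 50% of the previously reported median difference". The target is therefore 0.5 × 1.15 = 0.575, with about 55 evaluable per group. No SD is printed ("dispersion was approximated from the reported percentiles under an approximate normality assumption"), so the 55 cannot be reproduced independently. Solving n = 2·SD²·(1.960 + 0.842)²/0.575² for n = 55 gives SD = 0.575 × √(55/2) / 2.802 ≈ 1.076, a standardised target of 0.575/1.076 ≈ 0.534. The exact t-test version gives 0.539 (SD 1.067). This serves only as a yardstick below.

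**2. Direction.** Let H be a hypoxia score and r the correlation of S100B with H. The Introduction's premise is r > 0. Removing controls with high H lowers mean H among controls, and so lowers mean S100B. This does not depend on what FGR does.

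**3. Size, under assumptions.** Neither the share of controls removed (q) nor r is in the document. Assumed ranges: q = 5–20%, r = 0.2–0.7. With H and S100B normal and the worst fraction q removed from controls only, the shift in SD units is

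shift = r × φ(z) / (1 − q), where z is the upper-q point of the standard normal.

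- q = 5%: φ(1.645)/0.95 = 0.1031/0.95 = 0.109. With r = 0.2, shift 0.022.
- q = 10%: φ(1.282)/0.90 = 0.1755/0.90 = 0.195. With r = 0.3, shift 0.058.
- q = 20%: φ(0.842)/0.80 = 0.2800/0.80 = 0.350. With r = 0.7, shift 0.245.

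**4. Effect on the test.** A t-test was simulated with 55 per group, 20,000 runs and no true FGR effect. The nominal level is 5% two-sided, so 2.5% for falsely finding S100B higher in FGR.

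| Removed (q) | r | Shift, SD | Share of 0.575 target | Two-sided rejection | Rejection as higher in FGR |
|---|---|---|---|---|---|
| 5% | 0.2 | 0.022 | 4% | 5.2% | 3.2% |
| 5% | 0.3 | 0.033 | 6% | 5.3% | 3.6% |
| 10% | 0.3 | 0.058 | 11% | 6.3% | 5.0% |
| 10% | 0.5 | 0.097 | 18% | 8.0% | 7.4% |
| 20% | 0.5 | 0.175 | 33% | 15.1% | 14.9% |
| 20% | 0.7 | 0.245 | 46% | 26.9% | 26.8% |

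With the same exclusions in both groups, or with none of them in either, the shift is 0 and the level returns to 5%.

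**The case against.** **The design is disclosed and deliberate.** The article says controls should be healthy and explains why FGR infants are treated differently. It limits its claims to associations, and healthy controls are a legitimate reference group. This stands as far as it goes: FGR versus healthy, non-hypoxic neonates is a coherent contrast. But objective 1 and Trial design do not describe that contrast, the baseline sentence claims more, and the limitations mention patients lost through exclusions but not this selection.

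**An analysis plan may hold a sensitivity analysis.** It may, and its absence from the article is not the point. The point is a statement in the text that is wrong for the objective as worded.

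Four stronger readings are tempting, and the document does not support them:

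- *The birth-weight limits add to the bias.* They verify that controls grew normally, as Trial design requires. The Introduction reports higher S100B in FGR or SGA newborns (with some contradictory findings), so re-admitting controls below the 10th percentile could blur the contrast.
- *All excluded controls should return as the primary control set.* Mothers were told such children would be disqualified. Ethics and dissemination requires a formal amendment for changed criteria, and about two-thirds of the target was enrolled by September 2025. The statement that "data from excluded patients will be retained to support further analysis" does not help: it follows the sentence on patients with no cord sample, who have no S100B value.
- *The false-positive rate is known to be high.* It is not. At the low end of the assumed range the distortion is negligible. Study setting reports more exclusions than expected, but not by group or reason.
- *The biomarker's discrimination is inflated.* This is not shown. Objective 3 assesses discrimination against pH, BE and lactate, not FGR against control.

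**Conclusion.** The concern holds, limited to the control-only pH, BE, Apgar, CTG and hypoxia-risk criteria. On the protocol's own premise that S100B rises with hypoxia, these criteria push the primary contrast towards S100B being higher in FGR, and nothing in the planned group test offsets this. If the premise were false the bias would vanish, but so would the case for the biomarker.

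The size is not known. The range of about 0.02–0.25 SD (4–46% of the target difference), with two-sided type I error of about 5–27%, rests wholly on assumed q and r, on normality and on a single hypoxia score. The trial need not be redesigned. What must change is what objective 1 is said to show, supported by one further analysis.

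**What to change.** 1. **Symmetric analysis.** Before S100B results are analysed, prespecify a comparison of the controls with those FGR infants who meet the same pH, BE, Apgar and CTG limits, reported beside the primary test. Cord gases and Apgar are already collected in both groups. CTG is not named in the data-collection list and may have to be taken from the records. The FGR subset will be smaller, and the analysis conditions on possible mediators. It therefore shows whether a difference persists without overt hypoxia, and is not a total FGR effect.

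2. **Wording.** Restate objective 1 and its conclusion as FGR versus healthy, non-hypoxic neonates. Replace the baseline sentence with one saying that controls were selected for absence of hypoxia markers and FGR infants were not. Name this one-sided selection as a limitation, and report the number of controls removed by each criterion so that readers can judge q. The cost is text and a tally.

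3. **Optional sensitivity analysis.** Only where serum survives, and consent and the ethics committee allow, add the normally grown controls excluded solely on pH, BE or Apgar. The cost is a few assays and an amendment. It may not be feasible, since the article does not say whether serum of disqualified infants is kept.

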## Introduction

Fetal hypoxia-ischemia (HI) presents a major challenge in perinatology due to its potential for causing severe complications in the child. Hypoxemia can result in brain damage, which may lead to conditions such as cerebral palsy, epilepsy, delayed psychomotor development, intellectual disability, and cognitive impairment [1–3].

Currently, the diagnosis of neonatal HI relies on a combination of prenatal and postnatal data. Abnormal UA and MCA blood flow parameters detected prenatally may indicate a risk of fetal HI. Postnatally, the diagnosis is based on neurological examination, laboratory tests, neurophysiological assessments, and imaging studies (such as ultrasound and MRI), along with ultrasonographic evaluation of blood flow parameters in the MCA and anterior cerebral artery (ACA) [1,3]. Despite these methods, some infants with CNS damage may not show immediate symptoms or abnormalities in additional tests after birth, highlighting the need for improved early identification strategies. Cord blood biomarkers, such as the S100B, are therefore of significant interest [1–11].

S100B is a calcium-binding regulatory protein found in the cytoplasm of brain cells. In cases of CNS damage, such as hypoxia, S100B is released into the bloodstream, resulting in elevated levels in cerebrospinal fluid and umbilical cord blood [2,8,12]. This allows for the noninvasive assessment of the biomarker’s concentration immediately after birth. Due to its short half-life, S100B facilitates the recognition and monitoring of CNS damage progression, with its concentration correlating with the severity of hypoxia. Other factors that can elevate S100B levels in a newborn’s bloodstream and cord blood include chorioamnionitis, preterm birth, prolonged vaginal labor (lasting over 15 hours), and operative delivery [5,13–17]. Conversely, significantly lower S100B levels have been observed in infants born to mothers treated with selective serotonin reuptake inhibitors (SSRIs) [18].

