#### Study group – Exclusion criteria.

Antenatal (at recruitment):Maternal conditions that may affect the blood flow in placental vessels, including smoking, use of illicit stimulant substances, or pregestational diabetes.Maternal depression requiring pharmacological treatment (e.g., SSRIs).Intrapartum:Factors indicating a possible intrauterine infection, such as amniotic fluid leakage for more than 15 hours, spontaneous preterm labor, diagnosed intrauterine infection, or maternal symptoms of infection.Prolonged labor lasting more than 15 hours.

Given the data on increased S100B level in labor exceeding 15 hours, this duration of amniotic fluid leakage was set as the cutoff point in the exclusion criteria [5,17].

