### Study procedures and data collection

Data will be collected through cord blood samples, ultrasound measurements, and clinical assessments.

For all patients who consent to participate in the study, an ultrasound examination will be performed within 48 hours before delivery. This ultrasound assessment includes:

a. Measurement of the fetus’s anthropometric dimensions and estimation of fetal weight.b. Evaluation of blood flow using the pulsatility index (PI) in the UA, UtA, DV, and MCA.

After birth, in both the study and control groups:

A 1.5 ml blood sample will be collected from the clamped part of the umbilical cord:a. Immediate analysis: 0.5 ml of the cord blood will be sent immediately to the laboratory to determine pH, BE, and lactate levels in the umbilical cord blood analysis.b. S100B protein analysis: The remaining 1 ml of cord blood will be placed in a labeled tube (including the mother’s name, child’s gender, date of birth, and date of collection) and sent to the laboratory for centrifugation. Serum samples will be frozen at −20°C and stored. Once approximately 80 samples are collected, the serum will be thawed and analyzed for S100B protein concentration. Any remaining material after laboratory processing will be properly disposed of.Data will be collected on gestational age, duration, and mode of delivery, along with any complications encountered during delivery. Additionally, details regarding the newborn’s condition after birth will be recorded, including gender, Apgar score, and anthropometric measurements. Observations made during hospitalization will also be documented, with particular attention to any concerning symptoms related to the CNS, such as muscle tone abnormalities or seizures.A transfontanelle ultrasound examination will be performed to assess for any abnormalities in the newborn.

Study participation does not alter standard hospitalization procedures or duration. Furthermore, collecting a blood sample for the planned tests will not interfere with cord blood collection if the mother intends to bank it.

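### Balancing controls on the overall CS percentage does not control labour before CS or instrumental vaginal birth, and the S100B group comparison is unadjusted

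*Protocol article*

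**What the plan says.** All places are in the protocol article.

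- **Balancing rule** (last paragraph under Eligibility criteria, after the control group's exclusion criteria). The number of vaginal and CS births in the FGR group is monitored, and control recruitment is "adjusted based on the mode of delivery to ensure that the percentage of CS is similar in both groups". The stated purpose is to reduce confounding by delivery method. The factor is "the mode of delivery (vaginal delivery [VD] or cesarean section [CS"]), with no finer split.
- **Delivery factors said to raise S100B** (Introduction). The list includes "prolonged vaginal labor (lasting over 15 hours), and operative delivery". Operative delivery is not defined.
- **Long labour** (Exclusion criteria, both groups). The study group excludes "Prolonged labor lasting more than 15 hours". The control group has the same limit and adds a starting point: "Prolonged labor lasting more than 15 hours (counted from the onset of regular uterine contractions").
- **Exclusions for controls only** (Control Group – Exclusion criteria). These include "abnormal fetal blood flow parameters on ultrasound, abnormal CTG recordings", risk factors for perinatal hypoxia-ischemia, low Apgar scores and abnormal cord gases. The protocol explains that this difference is deliberate.
- **Data recorded** (Study procedures and data collection). "Data will be collected on gestational age, duration, and mode of delivery", together with complications of delivery.
- **Analysis** (Statistical methods). S100B is compared between groups by t-test or Mann-Whitney U. Mode of delivery and pregnancy duration are named as confounders only for regressions relating two continuous variables.

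**The concern.** The balancing step is meant to keep delivery-related S100B release from being mistaken for an FGR effect. A matched CS percentage does this only if CS births, and vaginal births, are alike in the two groups in whatever raises S100B. Each level mixes different exposures. A CS may come before any labour or after many hours of it, and a vaginal birth may be spontaneous or instrumental.

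The eligibility rules give a reason to expect a difference. A control delivered by CS or instrument because of an abnormal CTG is removed, while the equivalent FGR birth stays. The controls who fill the CS share then tend to be those without a fetal indication. If labour or instrumental birth raises S100B, part of the observed group difference would reflect delivery rather than growth restriction, in the direction of the study hypothesis. The group comparison as stated has no term that would remove this.

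**Working it through.** **Step 1: what is controlled and what is not.**

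| Delivery exposure | Handling in the protocol |
|---|---|
| CS versus vaginal | Balanced by recruitment |
| Labour over 15 hours | Excluded in both groups |
| CS before versus in labour | Not controlled |
| Labour up to 15 hours | Not controlled |
| Spontaneous versus instrumental vaginal birth | Not controlled |
| Operative delivery | Undefined: balanced if it means CS, not controlled as far as it includes instrumental birth |

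**Step 2: the planned effect in SD units.** The target difference is 0.5 × 1.15 = 0.575. Sample size gives no SD, so the figure of about 55 per group cannot be reproduced independently. Solving backwards (two-sided 0.05, power 80%, 55 per group, t-test) gives a standardised effect of 0.539 and an SD of 0.575 / 0.539 = 1.067. The value 0.539 is implied by the sample size; the protocol does not state it.

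**Step 3: size of a residual bias.** The article gives neither the shares of delivery subtypes nor their effects on S100B, so both are assumed:

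bias (SD) = difference between groups in the share of births exposed × effect of exposure (SD)

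The chance of p < 0.05 when FGR itself has no effect is 1 − Φ(1.96 − k) + Φ(−1.96 − k), where k = bias / √(2/55). Each cell shows the bias, its percentage of 0.539, and that chance.

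| Difference in share | Effect 0.25 SD | Effect 0.5 SD | Effect 1.0 SD |
|---|---|---|---|
| 10 points | 0.025; 4.6%; 5.2% | 0.05; 9.3%; 5.8% | 0.10; 18.6%; 8.2% |
| 20 points | 0.05; 9.3%; 5.8% | 0.10; 18.6%; 8.2% | 0.20; 37.1%; 18.2% |
| 30 points | 0.075; 13.9%; 6.8% | 0.15; 27.8%; 12.3% | 0.30; 55.7%; 35.0% |
| 40 points | 0.10; 18.6%; 8.2% | 0.20; 37.1%; 18.2% | 0.40; 74.2%; 55.5% |

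**Step 4: reading the range.** For labour before CS, the difference in share equals the CS share times the difference within CS. Suppose 40% CS in both groups, with 60% of FGR sections and 20% of control sections in labour (all assumed). The difference is 0.4 × 0.4 = 16 points. With an effect of 0.5 to 1.0 SD the bias is 0.08 to 0.16 SD, or 15% to 30% of 0.539. At the same CS share, a 40-point difference from this source alone would need every FGR section and no control section to be in labour. The bottom row is therefore an outer limit.

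**The case against.** Four objections have force.

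1. **The protocol claims less than a reader might infer.** It does not name labour in general, or operative vaginal delivery, as raising S100B. It names labour over 15 hours, which is excluded in both groups, and operative delivery without a definition. Nor is the balancing step the only safeguard, given that exclusion. This stands, and it narrows the point to the three uncontrolled rows in Step 1.
2. **The imbalance is not shown.** A reader might conclude that control sections will be mostly elective. No section gives CS timing or indication. CS in labour for a non-fetal reason remains open to controls, and FGR cases may also have CS before labour. This stands: the imbalance is plausible from the eligibility rules, and its direction is likely rather than established.
3. **Part of the difference may not be confounding.** CS for fetal compromise can result from FGR and belong to the hypoxic stress that S100B is meant to reflect. Adjusting for it could remove real signal. This stands, and it rules out replacing the unadjusted comparison with an adjusted one alone.
4. **Covariate coding is commonly left to an SAP.** This is true of coding. However, the article itself states an unadjusted test for the group comparison and a two-level factor for recruitment, so the gap lies in what is written.

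Quotas on four levels would also be hard to fill. About two-thirds of each group was enrolled by September 2025, which leaves about 60 / 3 = 20 controls to steer.

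**Conclusion.** The point holds in limited form. Matching the CS percentage leaves labour versus no labour, labour up to 15 hours, and instrumental birth uncontrolled within the two levels. The control-only exclusions make a difference between groups plausible, and the stated S100B comparison does not adjust for it.

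The size is not settled by the documents. Under the assumed shares and effects the bias is about 0.03 to 0.40 SD. A middle case (20 points, 0.5 SD) gives 0.10 SD, 19% of the implied effect and an 8.2% false-positive rate. It may be negligible or material. No single figure in the range, and no claim that the groups are in fact unbalanced, is supported by the text. This is a cheap improvement that serves the protocol's own stated aim; it does not invalidate the design.

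**What to change.** 1. Define operative delivery where the Introduction cites it, stating whether it means CS, instrumental vaginal birth or both.
2. Code delivery as CS before labour, CS in labour, spontaneous vaginal or instrumental vaginal. Collapse sparse levels, or use mode plus labour duration. If duration is used, count it from the same starting point in both groups; at present only the control criteria state one.
3. Report the distribution of these levels by group.
4. Pre-specify an S100B group comparison adjusted for this factor, shown beside the unadjusted one. The linear or quantile regression already named in Statistical methods will serve. State that CS for fetal compromise may be a consequence of FGR, so the adjusted estimate may be conservative.
5. Steering the remaining control recruitment by these levels is optional.

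The cost is recoding data on duration, mode and complications of delivery, with a check that CS timing and instrumental birth can be read from them, and a few sentences of text. The downside is some small cells and slightly wider intervals for the adjusted estimate.
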